**Table 2 Tab2:** **Blood sample time-points (T) according to immunological sub-study**

	**Blood sample T1 (first week of life)**	**Blood T2 (6 weeks of age)**	**Blood sample T3 (6 weeks of age)**	**Blood sample T4 (10 weeks of age)**
Cytokine sub-study	5 days after birth	Immediately before primary immunisations	5 days after primary immunisations	Immediately before primary immunisations
Iron sub-study	5 days after birth	1 day after primary immunisations	5 days after primary immunisations	1 day after primary immunisations
Epigenetic sub-study	5 days after birth	Immediately before primary immunisations		

### Stool samples

Stool samples will be collected at the 6-week and 10-week time-points and stored to allow for future analysis, funding permitting.

### Other samples collected

Whenever an unwell participant presents to the study team investigations and treatments will be conducted as directed by the attending clinician. Investigations will include cultures for accurate diagnosis of febrile illness. An extra 2-ml blood sample will be taken from any participant under-going phlebotomy provided that this will not compromise the child’s health or well-being. This will allow a sub-study to be conducted to compare primary immunological outcomes in unwell children according to BCG status.

### Laboratory procedures

#### Cytokine sub-study

Overnight whole blood stimulation with the non-specific stimulants *S. aureus, S. pneumoniae, E. coli, C. albicans* and polyinosinic:polycytidylic acid/C-phosphate-G (Poly I:C/CpG) will be carried out using fresh sodium-heparinised blood. Measurement of the pro-inflammatory cytokines IL-1β, IL-6, TNF-α and IFN-γ by ELISA (BD-OptEIA, Becton, Dickinson and Company, Oxford, UK) will then be conducted on the harvested supernatant following storage at −80°C. These stimulants have been chosen because they are the most common pathogens isolated from septic neonates in Uganda [49] and because they represent a range of pathogen types and toll-like receptor pathways.

#### Epigenetic sub-study

The levels of trimethylation of H3K4 at the promoter region of pro-inflammatory cytokines will be assessed using chromatin immunoprecipitation followed by qPCR. Peripheral blood mononuclear cell (PBMC) isolation for this work will occur by density-centrifugation over histopaque (Sigma-Aldrich, Dorset, UK).

#### Iron sub-study

Measures of iron status will be conducted on the plasma fraction of lithium-heparinised blood following storage at −80°C. Serum iron, Unbound Iron Binding Capacity (UIBC), Total Iron Binding Capacity (TIBC), Transferrin Saturation (TSAT) and ferritin will be measured using the automated Cobas Integra (Roche Diagnostics, Switzerland). The hormone hepcidin will be quantified using ELISA (Bachem-25, Bachem, Switzerland).

Red cell parameters will be measured from fresh EDTA whole blood using a Coulter A^**C.**^T 5 Diff CP haematology analyser (Beckman Coulter, Inc, CA, USA).

### Primary outcomes

#### Cytokine sub-study

IL-1β, IL-6, IL-10, TNF-α and IFN-γ cytokine levels following *in-vitro* stimulation with *S. aureus, S. pneumoniae, E. coli, C. albicans* and Poly I:C/CPG*.*

#### Epigenetic sub-study

H3K4 trimethylation at the region of pro-inflammatory cytokines in peripheral blood monocytes

#### Iron sub-study

Hepcidin levelsTSAT

Primary outcomes in each sub-study will be compared between the 2 intervention groups both acutely following BCG (up to 1 week after birth/6 weeks of age) and at time-points distant from vaccination (6 and 10 weeks of age).

### Secondary outcomes

Physician-diagnosed infectious diseaseParental-reported infectious diseaseCulture-positive infectious diseaseMortality

The above clinical outcomes for the three sub-studies will be analysed together to increase power.

The iron sub-study will also have the following secondary outcomes:Serum ironTIBCFerritinTransferrinHaemoglobinRed cell parameters

In a secondary analysis, longitudinal within-infant changes in primary outcomes will also be analysed for each sub-study.

### Sample size considerations

Each sub-study is powered for its own primary outcomes. The overall sample size is the summation of the participants required for each sub-study.

#### Cytokine sub-study: n = 240

Due to paucity of published data in this area, an approach based on standard deviation (SD) difference in average population cytokine levels has been used. Forty-eight subjects per intervention group (BCG immunisation at birth or at 6 weeks of age) will be needed at each time point to show a 0.66 SD difference in average population cytokine levels with 90% power and 5% significance. Sixty infants per intervention group per time point will be recruited to allow for attrition. As each recruited infant will be bled at 2 time-points, 240 infants will be recruited in total to allow for the 4 time-points.

#### Epigenetic sub-study: n = 80

The only previous study in this area (which was performed in adults) required 20 subjects per intervention arm [47]. We will recruit 40 subjects to each intervention arm to allow for attrition and also due to the requirement for a full 2-ml blood sample for epigenetic analysis, which is unlikely to be obtained for all subjects. Due to funding constraints, epigenetic analysis will be restricted to the first two sampling time-points, and each infant will be bled at both time-points, eighty subjects will be recruited in total.

#### Iron sub-study: n = 240

Sample size determination was performed using TSAT as it is the only primary outcome parameter currently of clinical relevance. Average neonatal TSAT in low-income settings is 55% [50]. Fifty infants in each group at each time point will be needed to show a 30% reduction in transferrin saturation (reduction to average TSAT levels in low income settings) with 90% power and 5% significance. Sixty subjects will be recruited to each intervention group at each time point to allow for attrition. As each recruited infant will be bled at 2 time-points, 240 infants will be recruited in total.

#### Overall sample size: n = 560

Combined analysis of clinical end-points from all three sub-studies will be conducted as secondary analysis. Based on data from a previous study in Entebbe [51] we expect 80% power to detect a ≥ 40% reduction in physician-diagnosed invasive infections with 5% significance. The effect of BCG is unlikely to be this pronounced, but this preliminary data combined with the primary immunological outcomes, should provide sufficient evidence to determine whether expanding the cohort would be valuable.

### Data management

#### Description of the data

This is a randomised controlled trial with datasets generated from clinical questionnaires and laboratory assays. A combination of direct electronic capture and paper forms will be used, linked by a unique participant identifier. Microsoft Access (Redmond, WA, USA) will be utilised to produce the study database. Data will be exported from Microsoft Access to Stata (StataCorp, College Station, TX, USA) for statistical analysis.

#### Quality assurance

A detailed data dictionary with range checks will be used to reduce data entry errors. Quality control checks will be run by the data clerk, on a weekly basis, who will highlight any queries to the principal investigator. Data will only be uploaded onto the master database once any queries highlighted by quality control checks have been resolved.

### Statistical analysis

Group characteristics will be compared using Pearson’s Chi-squared test for categorical variables and the *t*-test for continuous variables. Cross-sectional comparisons between intervention groups at each time-point will be carried-out using the *t*-test for differences between means. Non-normally distributed outcome data will be log-transformed before analysis; Mann–Whitney two-tailed test will be used for persistently skewed data. If potential confounders remain unbalanced between the groups despite randomisation: for instance season of birth, these will be adjusted for using multiple linear regression analysis. Paired/longitudinal analysis of within infant changes in parameters over time will be conducted using the paired student *t*-test or Wilcoxon matched-pairs test. Incidence rate of invasive infectious disease in the first 10 weeks of life will be compared by Poisson regression with a random effects model to allow for within-child clustering. Statistical significance will be assessed at the 2-sided 0.05 level but interpretation of results will not be solely reliant on *P*-values.

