### Study design

This study is an investigator-blinded randomised controlled trial of BCG vaccination given at birth versus BCG vaccination given at 6 weeks of age. Cord blood and two venous blood samples will be collected from participants to allow comparison of innate immune system parameters. All participants will be clinically followed-up until 10 completed weeks of age, to allow comparison of illness outcomes. This study design will allow comparison of outcomes between BCG-naïve and -vaccinated infants up to 6 weeks of age, and early with delayed BCG-vaccinated infants from 6 to 10 weeks of age, helping to identify whether there is a critical period for BCG-induced non-specific effects. The time-point of 6 weeks for the delayed BCG group has been chosen as it is the longest delay possible prior to the potential confounding influence of primary immunisations.

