### Intervention and randomisation

All infants will receive 0.05 ml of BCG-Statens Serum Institute (SSI, Copenhagen, Denmark) (Danish Strain 1331) intra-dermally into the right deltoid. This will be given either at birth (Early intervention arm) or at 6 weeks of age (Delayed intervention arm).

Intervention and blood sampling time-point allocation will be determined by block randomisation, stratified by sex. This will be carried out by an independent statistician, prior to the trial commencement, using Stata (StataCorp, College Station, TX, USA) to generate the allocation sequence. Allocations will be concealed within sequentially numbered, sealed opaque envelopes, prepared by two research assistants who are independent of the trial. Upon delivery of an eligible infant, assignment of allocation will be carried out by midwives who will select the next sequential envelope according to the infant’s gender.

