### Blood samples collected

All participants in the study will have 10 ml placental cord blood collected at birth; divided into 5 ml of heparinised and 5 ml of ethylenediaminetetraacetic acid (EDTA)-anticoagulated blood. They will then have 2-ml venous blood samples collected at 2 time-points between birth and their exit from the study at 10 completed weeks of age. Each sub-study has up to four possible time-points where blood samples are collected, but each infant will only be bled at two of these time-points (randomly allocated) to avoid undue stress for the baby and the mother. The time-points have been selected to enable interrogation of the changes to the innate immune system induced by BCG both acutely following vaccination and in the longer term. The timing of the blood samples in the iron sub-study differs slightly from those in the cytokine and epigenetic sub-studies (see Table 2). These differences are necessitated by the systemic nature of iron metabolism. As hepcidin is produced mainly in the liver this precludes analysis of iron metabolism following *in-vitro* non-specific stimulation. Thus, the iron sub-study will use routine primary immunisations as *in-vivo* non-specific stimuli and measure the resulting changes to iron parameters.

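### The stated primary between-arm analysis uses neither the cord-blood sample required of every infant nor the sex stratifier, and adjusts only for confounders that turn out unbalanced

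*Protocol article*

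**What the plan says.** All references are to the protocol article.

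- **Primary test (Statistical analysis).** "Cross-sectional comparisons between intervention groups at each time-point will be carried-out using the" t-test. For skewed data, "Non-normally distributed outcome data will be log-transformed before analysis", and Mann–Whitney is the fallback if skew persists.
- **Adjustment (Statistical analysis).** "If potential confounders remain unbalanced between the groups despite randomisation", with season of birth as the one example, multiple linear regression is used. Earlier in the same section, "Group characteristics will be compared using Pearson’s Chi-squared test for categorical variables and the" t-test for continuous ones.
- **Within-infant change.** "Paired/longitudinal analysis of within infant changes in parameters over time will be conducted using the paired student" t-test or the Wilcoxon matched-pairs test. The Secondary outcomes section labels this a secondary analysis.
- **Cord blood.** Under Blood samples collected, "All participants in the study will have 10 ml placental cord blood collected at birth". Eligibility criteria exclude an infant whose cord blood is not obtained, and the Overview of study procedures places collection before randomisation. Study design gives the purpose: "Cord blood and two venous blood samples will be collected from participants to allow comparison of innate immune system parameters".
- **Stratification (Intervention and randomisation).** Allocation is by "block randomisation, stratified by sex".

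**The concern.** A baseline sample is required of every infant before allocation, and allocation is stratified by sex. Neither appears in any stated between-arm analysis. The paired tests do not fill the gap: they assess change within infants and are not a baseline-adjusted comparison of the arms.

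Three things are at stake.

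1. **Precision.** The cross-sections are small (48 to 50 per arm needed in the cytokine and iron sub-studies), so a baseline correlated with the outcome is worth having.
2. **Correct standard errors.** Stratification balances sex between arms. If sex predicts the outcome, a test that ignores it counts the sex variation as noise and overstates the standard error.
3. **A fixed model.** Adjusting only for what looks unbalanced ties the model to the observed data. It is also least likely to pick sex, which stratification keeps balanced, and it selects on imbalance rather than on prognostic value.

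**Working it through.** **Inputs.** From Sample size considerations, cytokine sub-study: 48 per arm per time-point, 0.66 SD, 90% power, 5% significance. Two-sided testing is from Statistical analysis. The correlation r between a cord value and the later value of the same parameter is not given, so a range of 0.2 to 0.7 is assumed. The size of any sex effect is not given either; 0, 0.5 and 1 SD (within-sex SD) are assumed.

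**Step 1: reproduce the plan's figure.** n per arm = 2 × ((1.960 + 1.282) / 0.66)² = 48.24, against the stated 48. Normal-approximation power at 48 is Φ(0.66 / √(2/48) − 1.960) = Φ(3.233 − 1.960) = 0.899; exact noncentral-t power is 0.893. The sample size is therefore that of an unadjusted two-sample test.

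**Step 2: adjust for the cord value.** The residual SD becomes √(1 − r²).
- Effective sample size is multiplied by 1 / (1 − r²).
- Power = Φ(0.66 / (√(1 − r²) × √(2/48)) − 1.960).
- Difference detectable with 90% power = 3.242 × √(1 − r²) × √(2/48).

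| r (assumed) | Gain in effective n | Power at 0.66 SD | Detectable difference |
|---|---|---|---|
| 0 | 0% | 0.899 | 0.66 SD |
| 0.2 | 4% | 0.910 | 0.65 SD |
| 0.3 | 10% | 0.924 | 0.63 SD |
| 0.5 | 33% | 0.962 | 0.57 SD |
| 0.7 | 96% | 0.995 | 0.47 SD |

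**Step 3: omit the stratifier.** Take arms balanced within sex, equal numbers of each sex and a sex effect of b SD. The t-test's standard error is then too large by the factor √(1 + b²/4).
- b = 0.5: factor 1.031. Type I error = 2 × (1 − Φ(1.031 × 1.960)) = 0.043. Power = Φ(3.233 − 2.020) = 0.887.
- b = 1: factor 1.118. Type I error = 2 × (1 − Φ(1.118 × 1.960)) = 0.028. Power = Φ(3.233 − 2.191) = 0.851.
- b = 0: no loss.

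A simulation (48 per arm, 4,000 runs per scenario) agrees. At b = 1 the t-test had type I error 0.026 to 0.031 and power 0.840 to 0.851. The model with cord value and sex had power 0.916, 0.960 and 0.996 at r = 0.3, 0.5 and 0.7. Over all nine scenarios that model's simulated type I error ranged from 0.043 to 0.062 around the nominal 0.05.

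**Step 4: adjust only when unbalanced.** The article gives no criterion, so the simulation assumed adjustment for the cord value when its baseline test gave p < 0.05. With no sex effect, power was 0.897, 0.900 and 0.909 at r = 0.3, 0.5 and 0.7, against 0.919, 0.953 and 0.996 for the prespecified model. Type I error was 0.035 to 0.049. Under this assumed trigger, almost none of the gain is recovered.

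**The case against.** The strongest reply is that nothing is broken. A two-sample t-test in a randomised comparison is valid, and the sample size was set for exactly that test. At 0.66 SD the trial already has about 90% power, so a low correlation adds only 1 to 2.5 percentage points. All of this stands, and it makes the point one of efficiency and prespecification.

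Three further objections limit what can be claimed:

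- **Cord values complete by design.** A reader might infer this from the exclusion criterion. The criterion ensures only that a sample is obtained. Table 2 lists venous time-points, and no section says that each primary assay is run on cord blood. Some cord values may be absent or fail.
- **A significant baseline test as the trigger.** A reader might infer this because both statements are in one section. The article does not link them, and it does not say whether the regression replaces or supplements the t-test. What it does state is that adjustment depends on imbalance seen after randomisation.
- **Sex as a predictor.** No section says that sex predicts these outcomes, so the loss from omitting it is conditional.

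It can also be said that a covariate list belongs in a statistical analysis plan not shown here. That is fair, and the missing list is not the complaint. The unadjusted primary test and the imbalance rule are stated choices.

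**Conclusion.** The point holds as a recommended improvement to a stated method. The planned comparison leaves out a required pre-randomisation sample and the stratifier, and makes adjustment depend on the data.

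The size rests on the assumed correlation: power of about 0.92, 0.96 and 0.995 at r = 0.3, 0.5 and 0.7, against about 0.90 unadjusted, with little gain at 0.2 or below. If sex is prognostic the t-test is conservative: type I error is about 0.043 for a 0.5 SD sex effect and 0.028 for a 1 SD effect.

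A reader might go further and infer that the primary comparison is biased or its false-positive rate inflated. The documents do not support that. Randomisation protects the unadjusted comparison, and leaving out the baseline or sex costs power without raising type I error. The remaining weakness is discretion: the reported primary estimate may be adjusted or not according to what the data show.

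**What to change.** Before the allocation code is broken, prespecify as the primary analysis at each time-point a linear model, on the log scale where needed, with:

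- arm;
- sex;
- the matching cord-blood value, for each parameter assayed on cord blood.

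Add two rules. Keep infants with a missing cord value by a missing-indicator or by mean imputation of the baseline, so that adjustment does not shrink the sample. For outcomes still skewed after transformation, use a rank-based ANCOVA or robust standard errors.

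Remove the imbalance trigger. Treat other covariates, such as season of birth, as prespecified sensitivity analyses. Keep the unadjusted t-test or Mann–Whitney test as supportive.

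Where a parameter is not assayed on cord blood, the model reduces to arm and sex, and removing the trigger still applies. The cost is about two degrees of freedom and a little more analysis work. Blinding lasts until the laboratory work is complete and the data are locked, so the change can be made without knowledge of allocation.

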**Table 1 Tab1:** **Objectives for immunological sub-studies**

**Sub-study**	**Primary objectives**	**Secondary objectives**
Cytokine sub-study	Cross-sectional comparison of IL-1β, IL-6, TNF-α and IFN-γ cytokine levels following overnight *in-vitro* stimulation with *S. aureus, S. pneumoniae, E. coli, C. albicans* and Poly I:C/CpG between the two intervention groups:	Longitudinal analysis of within-infant changes in innate cytokine production following *in-vitro* stimulation with *S. aureus, S. pneumoniae, E. coli, C. albicans* and Poly I:C/CpG.
	1. Shortly after birth intervention (BCG vaccination/no vaccination): Aim 1	
	2. Six weeks post-birth intervention (immediately prior to first dose of primary vaccination): Aim 2	
	3. Shortly after 6-week intervention (BCG vaccination/no vaccination): Aim 3	
	4. Three weeks post-6-week intervention (immediately prior to second dose of primary vaccinations): Aim 3	
Iron sub-study	Cross-sectional comparison of transferrin saturation and hepcidin levels between the two intervention groups:	Cross-sectional comparison of serum iron, total iron binding capacity, ferritin, transferrin, haemoglobin and red cell parameters at the above time-points.
	1. Shortly after birth intervention (BCG vaccination/no vaccination): Aim 1	Longitudinal analysis of within-infant changes to iron status following *in-vivo* non- specific stimulation (provided by primary vaccinations)
	2. Six weeks post-birth intervention (shortly after first dose of primary vaccination): Aim 2	
	3. Shortly after 6-week intervention (BCG vaccination/no vaccination): Aim 3	
	4. Three weeks post-6-weeks intervention (shortly after second dose of primary vaccination): Aim 3	
Epigenetic sub-study	Cross-sectional comparison of monocyte histone-3 lysine 4 trimethylation (H3K4me3) at the promoter region of pro-inflammatory cytokines between the 2 intervention groups:	Longitudinal analysis of within-infant changes in monocyte epigenetic modification.
	1. Shortly after birth intervention (BCG vaccination/no vaccination): Aim 1	
	2. Six weeks post-birth intervention (immediately prior to first dose of primary vaccination): Aim 2	

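### The secondary longitudinal analyses use within-infant paired tests with no comparison of arms, so change with age cannot be separated from a BCG effect; iron, with no sample shortly before a dose, is the sharpest case

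*Protocol article*

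**What the plan says.** Under Secondary outcomes the protocol states: "In a secondary analysis, longitudinal within-infant changes in primary outcomes will also be analysed for each sub-study". Table 1 lists such an analysis as a secondary objective of the cytokine, iron and epigenetic sub-studies. The method is in Statistical analysis: "Paired/longitudinal analysis of within infant changes in parameters over time will be conducted using the paired student" t-test or the Wilcoxon matched-pairs test. No other longitudinal method for the immunological outcomes is named.

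The primary comparisons are handled differently in the same section: "Cross-sectional comparisons between intervention groups at each time-point will be carried-out using the" t-test, with Mann-Whitney for data that stay skewed.

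For iron, Table 1 sets the secondary objective as "Longitudinal analysis of within-infant changes to iron status following" the in-vivo stimulus given by the primary vaccinations. Table 2 puts iron T1 at 5 days after birth, T2 and T4 at "1 day after primary immunisations" (6 and 10 weeks of age), and T3 at 5 days after the 6-week immunisations. Blood samples collected adds that "each infant will only be bled at two of these time-points (randomly allocated") and that "All participants in the study will have 10 ml placental cord blood collected at birth".

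**The concern.** The aims concern what BCG does to the innate immune response. A paired test has no arm term. Its null hypothesis is that the mean (or median) change over time is zero, and ordinary development over the first 10 weeks can make that false in both arms whatever the vaccination schedule. A significant paired result therefore says nothing specific about BCG. The randomised contrast, which is available for every infant with two samples, is not used.

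For iron there is a second difficulty. The objective attributes the change to the primary vaccinations, but the schedule has no value shortly before a dose from which to measure it. In the delayed arm, Table 1 also labels iron T3 as shortly after the 6-week intervention, so change up to T3 in that arm combines age, primary vaccines and BCG.

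**Working it through.** **1. The plan's own figure.** The nearest stated figure is the cytokine sample size: 48 per arm per time-point for 0.66 SD, 90% power, two-sided 5%.

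- n = 2 × ((1.960 + 1.282) / 0.66)² = 48.24, so 49 after rounding up. Power at 48 is 0.899. The figure is reproduced within rounding.
- Total: 60 per arm × 2 arms × 4 time-points / 2 samples per infant = 240, as stated.

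This sizes the cross-sectional comparison. No figure is given for the longitudinal analysis.

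**2. Behaviour of the paired test when BCG has no effect.** None of these settings is in the protocol; they are assumptions:

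- Outcome SD of 1 at each time-point, and the same age shift δ in both arms (0.25, 0.5 or 1.0 SD).
- Within-infant correlation ρ of 0.3 or 0.5.
- 20, 40 or 60 infants per arm. The 20 is 240 / 6 possible venous pairs / 2 arms, if pairs are allocated equally. The 60 is the number recruited per arm per time-point, available for change from cord blood.

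The SD of a change is √(2(1 − ρ)), and the paired test's noncentrality is δ√n / √(2(1 − ρ)). For n = 20, ρ = 0.3, δ = 0.25 this is 0.25 × 4.472 / 1.183 = 0.95. For n = 60, ρ = 0.5, δ = 0.25 it is 0.25 × 7.746 / 1 = 1.94. Simulated rejection rates for the paired t-test in one arm (10,000 replicates per setting):

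| n per arm | ρ | δ = 0.25 | δ = 0.5 | δ = 1.0 |
|---|---|---|---|---|
| 20 | 0.3 | 14.9% | 42.9% | 94.8% |
| 20 | 0.5 | 18.3% | 56.8% | 99.0% |
| 40 | 0.3 | 25.2% | 73.6% | 99.9% |
| 40 | 0.5 | 33.7% | 87.0% | 100.0% |
| 60 | 0.3 | 37.1% | 89.9% | 100.0% |
| 60 | 0.5 | 47.1% | 96.8% | 100.0% |

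With δ = 0 the paired test rejects in 4.7-5.1%, so it is valid for its own null. In all 18 settings of the table, a two-sample t-test of the change between arms rejects in 4.6-5.4%.

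**3. Iron schedule.** Take the doses at exactly 6 weeks (day 42) and 10 weeks (day 70). Iron samples then fall on day 0 (cord), 5 (T1), 43 (T2), 47 (T3) and 71 (T4).

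- Latest samples before the 6-week dose: cord (42 days before) or T1 (42 − 5 = 37 days before). Change across that dose spans 38 days (T1 to T2) to 47 days (cord to T3).
- Latest sample before the 10-week dose: T3, 70 − 47 = 23 days before and itself 5 days after the first dose. Change across that dose from a post-dose sample spans 24 days (T3 to T4) or 28 days (T2 to T4).
- T2 to T3 spans 4 days, but both samples follow the dose.

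By contrast, Table 2 places cytokine T2 and T4 immediately before the immunisations.

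**The case against.** The strongest defence is that this is a secondary analysis described as within-infant change, which is what a paired test measures. Inference about BCG rests on the primary between-arm comparisons, and the section adds that interpretation will not depend on P-values alone. That stands, and it limits the weight of the point. A between-arm model could also sit in an analysis plan that is not shown; but here the protocol names the tests, and those named do not compare arms.

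Four stronger readings are tempting and are not supported.

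- A reader might infer that iron has no pre-immunisation sample at all. Cord blood is taken from every infant, T1 falls at day 5, and Study design says "Cord blood and two venous blood samples will be collected from participants to allow comparison of innate immune system parameters". What is missing is a sample shortly before a dose. The article does not say outright that cord blood is assayed for iron.
- A reader might infer that the iron objective is wholly out of reach. If T2 and T3 are an allocated pair, that pair shows about 4 days of change after the dose with little ageing, though without a pre-dose value.
- A reader might infer that significance in one arm only will be reported as a BCG effect. No such rule is stated, nor that the paired tests are run separately by arm. With no arm difference, such a split has probability 2p(1 − p), where p is each arm's power: 50% at most (p = 0.5), and 2 × 0.95 × 0.05 = 9.5% at p = 0.95. Since it depends on an unstated rule, it is not counted in the size of this point.
- A reader might infer that longitudinal data are too sparse to use. The 20 per arm per venous pair rests on an assumed equal split, change from cord blood uses every infant sampled at a time-point, and in the epigenetic sub-study all infants are bled at both time-points.

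**Conclusion.** The point holds for the secondary longitudinal analyses of all three sub-studies. The named tests cannot distinguish a BCG effect from change with age. With a shared age shift and no vaccine effect, a within-arm paired test rejects in about 15-100% of trials over the assumed range, against about 5% for a between-arm test of change. The range depends on the assumed shifts, correlations and numbers; the absence of an arm term does not.

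For iron, change across a primary immunisation dose also carries roughly three and a half to nearly seven weeks of ageing (24 to 47 days, with doses at exactly 6 and 10 weeks), so change within an arm cannot be attributed to the primary vaccinations alone. The primary cross-sectional comparisons are unaffected. The documents do not say how the paired results will be interpreted, so the defect is that the analysis cannot answer the BCG question, not that a false claim is planned.

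**What to change.** In Statistical analysis, make the longitudinal inference a between-arm comparison of within-infant change. Use either ANCOVA of the later value on the cord-blood or other earlier value, or a mixed model with arm, time-point and their interaction and infant as random effect, using all samples. Report the arm difference in change with a 95% CI, and label within-arm paired results descriptive. Cord blood is the cleaner covariate because it precedes BCG in both arms; T1 is taken after BCG in the early arm, so where T1 is the earlier sample the mixed model is preferable.

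Restate the iron longitudinal objective as the between-arm difference in change in iron status from the earlier sample (cord blood or T1) to the post-immunisation sample. Add that change within an arm cannot be attributed to the primary vaccinations alone. Keep it a change: a difference between arms in post-vaccination level would only repeat the cross-sectional objectives already in Table 1.

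The cost is analysis wording only, with no new samples or visits, provided cord blood is assayed for the outcome concerned; the plan should confirm this for iron.

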**Methods:**

This trial will be an investigator-blinded, randomised controlled trial of 560 Ugandan neonates, comparing those receiving BCG at birth with those receiving BCG at 6 weeks of age. This design allows comparison of outcomes between BCG-vaccinated and -naïve infants until 6 weeks of age, and between early and delayed BCG-vaccinated infants from 6 weeks of age onwards. The primary outcomes of the study will be a panel of innate immune parameters. Secondary outcomes will include clinical illness measures.

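### The design sets out two clinical contrasts split at 6 weeks, but the only clinical analysis stated pools all 10 weeks and estimates neither of them

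*Protocol article*

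**What the plan says.** The Abstract (Methods) and Study design sections divide follow-up at 6 weeks. Up to that age, vaccinated infants are compared with naive infants. After it, the comparison is "between early and delayed BCG-vaccinated infants from 6 weeks of age onwards", which Study design gives as "early with delayed BCG-vaccinated infants from 6 to 10 weeks of age". Study design ties this division to illness outcomes and to finding out whether BCG has a critical period.

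The Statistical analysis section fixes one clinical comparison: "Incidence rate of invasive infectious disease in the first 10 weeks of life will be compared by Poisson regression with a random effects model". It mentions no period term and no division of follow-up.

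On power, Sample size considerations says "we expect 80% power to detect a ≥ 40% reduction in physician-diagnosed invasive infections with 5% significance", citing an earlier local study. It gives neither the control-arm rate nor the window to which the reduction applies. Under Secondary outcomes, "The above clinical outcomes for the three sub-studies will be analysed together to increase power".

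**The concern.** From week 6 both arms are vaccinated, so a single rate ratio over 10 weeks mixes two different comparisons. On a constant hazard, 4/10 = 40% of the follow-up comes from the second one.

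Convergence after week 6 is plausible on the trial's own reasoning. The Background argues that any mechanism must act quickly, with most protection in the first week after immunisation, and Aim 3 asks whether BCG at 6 weeks works much as BCG at birth does. Aim 4 concerns neonatal susceptibility, a period that lies wholly before week 6.

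The immunological primary outcomes are compared separately at acute and distant time-points. Only the clinical analysis loses the split. The clinical data, together with the immunology, are to inform whether the cohort is expanded, so a real early effect blurred by pooling could weaken that decision.

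**Working it through.** **Inputs.** Total 560 infants, half delayed, so 280 per arm (Sample size considerations; Ethics). Rate ratio (RR) 0.60 and power 80% (Sample size considerations). Test level: "Statistical significance will be assessed at the 2-sided 0.05 level". Six weeks of follow-up before the delayed BCG and four weeks after it (Intervention and randomisation; Study design). Assumed, because not given: no loss to follow-up and no between-child overdispersion.

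**The plan's own figure.** The 80% cannot be reproduced forward, because no event rate or window is stated. It can be solved backward. With e0 and e1 the expected events in the delayed and early arms:

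- SE(ln RR) = √(1/e0 + 1/e1); power = Φ(|ln RR|/SE − 1.96).
- 80% power at RR 0.60 needs |ln 0.60|/SE = 1.96 + 0.84 = 2.80, so SE = 0.511/2.80 = 0.182.
- With e1 = 0.6·e0, SE² = 2.667/e0, so e0 ≈ 80 and e1 ≈ 48, or about 80/280 = 0.29 events per delayed-arm infant.

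**Pooled ratio.** Let f be the share of delayed-arm events that fall in weeks 0-6. Then pooled RR = f × 0.60 + (1 − f) × RR after week 6. With a constant hazard (f = 0.6) and RR 1.0 after week 6, this is 0.36 + 0.40 = 0.76.

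**Power if the 80% was computed on 10-week counts (e0 = 80.2 over 10 weeks).**

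- Pooled: e1 = 0.76 × 80.2 = 61.0; SE = √(1/80.2 + 1/61.0) = 0.170; 0.274/0.170 = 1.615; power about 37%.
- Weeks 0-6 alone: e0 = 0.6 × 80.2 = 48.1; e1 = 28.9; SE = 0.235; 0.511/0.235 = 2.17; power about 58%.

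**Power if it was computed on 0-6-week counts (e0 = 80.2 by week 6).**

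- Pooled: e0 = 80.2/0.6 = 133.7; e1 = 101.6; SE = 0.132; 0.274/0.132 = 2.09; power about 55%.
- Weeks 0-6 alone: 80% by construction.

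**Sensitivity to event timing (RR 0.60 to week 6, 1.0 afterwards).**

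| f | Pooled RR | Pooled power, 10-week basis | Weeks 0-6 power, 10-week basis | Pooled power, 0-6-week basis |
|---|---|---|---|---|
| 0.5 | 0.80 | 27% | 51% | 47% |
| 0.6 | 0.76 | 37% | 58% | 55% |
| 0.7 | 0.72 | 48% | 65% | 62% |
| 0.8 | 0.68 | 59% | 71% | 69% |
| 0.9 | 0.64 | 70% | 76% | 75% |
| 1.0 | 0.60 | 80% | 80% | 80% |

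**Sensitivity to the later effect (f = 0.6, 10-week basis).** RR after week 6 of 0.6, 0.8, 1.0 and 1.2 gives pooled power of 80%, 59%, 37% and 18%.

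**Detectable effect in weeks 0-6 on the 10-week basis.** With e0 = 48.1 and RR 0.50, e1 = 24.1, SE = 0.250 and 0.693/0.250 = 2.78, so power is Φ(0.82), about 79%. The 0-6-week contrast therefore has 80% power for about a 50% reduction.

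**The case against.** A reader might infer that the trial does not have the 80% power it states. The document does not support that. It attaches no window to the 40%, and if the 40% is the early-versus-delayed ratio over the whole 10 weeks, the 80% stands. Such a ratio does not require equal protection in both periods: at f = 0.6, an early RR of 0.33 followed by 1.0 gives 0.6 × 0.33 + 0.4 = 0.60. There is a precedent too. The Background reports the motivating trial's mortality ratio of 0.55 over the first 2 months, with the control arm vaccinated at about 6 weeks on average, so that effect already spans the control arm's vaccination.

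A reader might also infer that the pooled analysis is invalid. It is not. It compares randomised strategies, and vaccination timing is a stated interest of the trial.

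Several further points stand. The endpoint is secondary. The article says the true effect is unlikely to be this large and concedes limited power for clinical outcomes. Splitting does not restore 80% power if the original calculation used 10-week counts. The wording of the modelled outcome, invasive infection against the listed infectious disease outcomes, is a minor labelling matter, since invasive infection can be read as a subset of physician-diagnosed disease.

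It can also be said that period terms belong in an analysis plan not shown here. That carries less weight. The article does not leave the window open: it names one, and that window does not match the contrasts its own design section describes.

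**Conclusion.** The mismatch between design and analysis is real. Two period-specific clinical contrasts are set out, and the single stated model delivers neither and cannot identify a critical period. How far the pooled ratio is diluted, as an estimate of vaccinated versus naive, depends on two unknowns: when events occur and whether an early-versus-delayed difference persists. Under a constant hazard and full convergence after week 6, an RR of 0.60 becomes 0.76, and the pooled analysis has about 37% power against 58% for weeks 0-6, or 55% against 80%, depending on the basis of the stated power. With no convergence there is no dilution. All of these figures assume 280 per arm, no loss and no overdispersion. Because the endpoint is secondary and its limits are acknowledged, this is an inexpensive improvement to a stated analysis, not a flaw that undermines the trial.

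**What to change.** In Statistical analysis, split each infant's person-time at the 6-week intervention, using the same cut in both arms, and fit arm by period in the same random-effects Poisson model. Report the 0-6-week rate ratio as vaccinated versus naive and the 6-10-week ratio as early versus delayed. Keep the 0-10-week ratio as the overall comparison of timing strategies.

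In Sample size considerations, state the control-arm rate and the window to which the 40% and 80% apply. If the 80% was based on 10-week counts, add that the 0-6-week contrast has 80% power only for about a 50% reduction.

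The cost is a change of wording and, possibly, a less favourable stated detectable effect. Nothing new has to be collected. The downside is fewer events and wider intervals within each period.
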